## 1. Background

Reproductive genetic carrier screening (RGCS) is a form of genetic testing that provides prospective parents with information about their chance of having children with severe autosomal recessive and X-linked genetic conditions, thus promoting choice and reproductive autonomy [1,2]. While individually rare, it is estimated that 1–2% of reproductive couples have an increased chance of having children impacted by such conditions [3,4]. Such couples (henceforth referred to as ‘increased chance couples’) may choose to access reproductive options either to avoid, or to plan and prepare for the birth of children with the condition in accordance with their values [5]. These options include prenatal diagnosis (PND), in vitro fertilization (IVF) with preimplantation genetic testing for monogenic disorders (PGT-M), using donor gametes, adoption/fostering or not having children. 

Families can comprise a broad range of structures, and parents may or may not have genetic links with their child (for example, if gamete or embryo donors are used). With respect to RGCS, there are two ‘genetic parents’ (of male and female sex) for the prospective or current pregnancy who can be considered the ‘reproductive couple’. It is important to acknowledge non-genetic parents who may also be involved in the RGCS process with respect to pre-test deliberation and reproductive decision-making. Thus, when referring to ‘couples’ engaging in RGCS, we refer to the collective group who will use the information gained from RGCS to inform future reproductive choices. 

In the past, RGCS was primarily offered to those from certain ethnic backgrounds with a high disease prevalence. However, the recessive nature of these conditions, barriers in family communication of genetic information, and delayed or underdiagnosis of genetic conditions mean most affected children are born to parents who have no known prior history of the condition [6]. Additionally, as populations become increasingly multiethnic, relying on ethnicity ceases to be an effective way to guide offers of RGCS [7,8]. Numerous peak bodies now recognize RGCS as relevant to all people planning a pregnancy or in early pregnancy regardless of family history or ethnicity [9,10,11].

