### 2.4. Study Design

The MM study design is outlined in Figure 2. The study commenced in 2019 with an initial plan to recruit 10,000 couples and a completion date of December 2021. However, the SARS-CoV-2 pandemic impacted recruitment and laboratory testing. Thus, the study was extended with a revised recruitment target of 8350 couples and a completion date of December 2022. A longer-term follow-up of the reproductive outcomes will be undertaken in subsequent years. 

The study comprises three phases: (**1) Pre-implementation**, which involved study design and development (2019); (**2) Implementation**, which comprises the two stages of (*2a) Piloting and early implementation* (2020), and (*2b) Nation-wide implementation* (2021–2022); and (**3) Post-implementation**, assessing outcomes (2022 and beyond). The recruitment of couples was designed to occur in a staged manner, with the rate of recruitment increasing progressively over the course of the study. In Phase 2a, screening was offered in four states/territories: the Australian Capital Territory (ACT), New South Wales (NSW), Victoria (VIC) and Western Australia (WA). In Phase 2b, screening was extended to all Australian states and territories, including the Northern Territory (NT), Queensland (QLD), South Australia (SA) and Tasmania (TAS).

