Previous studies show that HCPs who currently provide pre- and early pregnancy care are ideally placed to introduce the notion of RGCS, but that time, a lack of knowledge about RGCS, and competing priorities are barriers to them offering RGCS [38,39]. To address these challenges, an online portal was developed for participant enrollment, education and consent, thereby reducing the requirements of rHCPs to provide detailed information about RGCS. Eligibility criteria were designed to be deliberately broad to enable a wide range of people to take part (Table 1). An effort has been directed to ensure that the study is accessible to people from a broad spectrum of ethnicities, including Aboriginal and Torres Strait Islander people, people with limited English, those without computer/Internet access and those with disabilities. People who already know that they have an increased chance of having children with a serious genetic condition (due to family history and/or previous genetic testing) are included in the study so they can access RGCS for other conditions. 

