#### 2.5.6. Designing the Reproductive Genetic Carrier Screen and Establishing Screening Processes

A key element in the pre-implementation phase was designing the MM RGCS and establishing the screening process. A simultaneous screening approach was chosen to enable the screening of both reproductive partners at the same time, with a report providing a combined assessment of reproductive risk for the reproductive couple. Using this approach, individual genetic carrier status for autosomal recessive conditions is not reported [54,55]. This is based on the observation that, when screening for a large number of genes, most people are genetic carriers for at least one condition [56], but the majority (around 98%) of reproductive couples are not genetic carriers for the same condition(s); thus, together, they have a low chance of having children with the conditions screened. With a large gene list, the individual analysis and reporting of individual genetic carrier results is burdensome for laboratories and would create a heavy demand on genetic counseling services. For example, one study showed the median time to provide genetic counseling to an individual following expanded RGCS is 64 min [57]. Limiting the reporting of variants to couples identified to have an increased chance of having an affected child allows the focus of resources to be directed toward those couples who can benefit the most from the screening. For X-linked conditions, an analysis is performed for the female member of the couple, as this result allows for the assessment of the chance of an X-linked condition affecting their children. There are very rare, X-linked conditions for which males typically have mild to no clinical features, whereas females can be severely affected; for example *EFNB1*, which is associated with craniofrontonasal dysplasia and is included in the MM gene list. There are also some genes located in the pseudoautosomal regions of the X and Y chromosomes, for example *SHOX*; biallelic pathogenic variants are associated with Langer mesomelic dysplasia and the gene is included in the MM gene list. These regions are the same in both the X and Y chromosomes and, from an inheritance perspective, behave as though they are on one of the autosomes (chromosomes 1–22), making it necessary to analyze the data from both partners, as for autosomal recessive conditions. 

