To minimize barriers, screening was designed to be performed on mouth swab samples, which could be posted directly to the reproductive couple and returned by mail. The mouth swab sample kits include user-friendly instructions and a link to a video demonstrating how to self-collect the sample. This approach is a convenient, pain-free sampling method, enabling couples to consider RGCS and provide samples in their own time. This approach also ensured that paired samples are received at the same time, reducing the requirement in the laboratory for storing and matching samples at a later date, as well as having to contact either member of the couple to remind them to send in their samples. Additionally, the quantity and quality of DNA obtained from the swabs is confirmed to be sufficient for all required tests, with a low rate of failure and an infrequent need for recollections. A process was established to assess family and personal history information provided by participants, to ensure the RGCS is appropriate for those couples for whom there is a family or personal history of a condition associated with a gene on the MM gene list. A section was included in the electronic study database to enable the collection of information about the RGCS results and details on variant curation.

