##### Quantitative Analysis

Quantitative data will be analyzed using the statistical software packages, STATA 16 and SPSS. Descriptive statistics will be used to summarize the program outcomes including the RGCS uptake, frequency of increased chance couples and reproductive decisions made by these couples. Detailed participant characteristics will be reported, with the representativeness of the participant sample compared to Australian population data assessed using a minimum dataset (e.g., socioeconomic status via the Index of Relative Advantage and Disadvantage quintile).

Data will be summarized using descriptive statistics (e.g., means, standard deviations, medians, interquartile ranges, frequency distributions and 95% confidence intervals). Inferential analysis will include univariable analysis such as χ^2^ and Fisher exact tests, unadjusted logistic regressions for categorical outcomes, and independent, two-tailed *t*-tests or non-parametric Mann–Whitney U tests for continuous outcomes. A comparison between participants who had RGCS and participants who did not proceed with RGCS after initiating enrollment will be performed using multivariable logistic regression, adjusting for significant covariates (*p* < 0.1 in the univariable analysis).

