##### Health Economic Analysis

A cost-effectiveness analysis will be conducted taking the costs to the healthcare system as the perspective. A decision tree model with probabilities based on outcomes from MM, costs from the Medicare Benefits Schedule and Pharmaceutical Benefits Schedule, and published data on lifetime costs of disease will be developed. Costs to the health system include the costs associated with IVF decisions, termination of pregnancy, and the expected future healthcare costs of maintaining a live birth with a severe inherited genetic condition. All costs will be standardized to 2022 values. The AQoL-4D will be scored using the Australian values [47] for both parents to identify any changes in quality of life over the 12 months of follow-up. A hypothetical comparator will be used to estimate costs and outcomes for the counterfactual of ‘usual care in the absence of the MM program’. This counterfactual will assign quality of life weights to both parents using population norms [68]; for those parents who have a live birth of a child with a genetic condition, a lower quality of life weight identified from MM and the literature will be assigned for the duration of the expected survival of the child. A quality of life weight for the child with a genetic condition will also be assigned for their expected survival. Quality of life and survival will be combined into quality-adjusted life years (QALYs). All future expected costs and QALYs will be converted into today’s values, discounted using a 5% rate based on Australian policy requirements, as stipulated by MSAC [65]. The difference in QALYs and costs for the MM participants and the counterfactual will be calculated and reported as an incremental cost-effectiveness ratio. TreeAge Pro (2018) will be used in this analysis.

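### Couples who already know their increased chance are enrolled, but the reporting rule, the frequency summary and the decision tree do not separate newly found from previously known results

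*Protocol article*

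**What the plan says.** Section 2.5.2 of the protocol article says of "People who already know that they have an increased chance of having children with a serious genetic condition", through family history or earlier testing, that they "are included in the study so they can access RGCS for other conditions". The same section names genetics and fertility services among the possible recruitment settings. It sets recruitment targets by geography and by public or private care.

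Section 2.6.4 issues an increased chance result when reportable pathogenic or likely pathogenic variants are found in the same autosomal gene in both partners, or in an X-linked gene in the female partner. No exception is stated for a gene already known in that couple.

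Section 2.7.1 (Quantitative Analysis) summarises the "frequency of increased chance couples and reproductive decisions made by these couples". Section 2.7.1 (Health Economic Analysis) plans "A decision tree model with probabilities based on outcomes from MM" and compares it with a hypothetical arm of usual care without the programme.

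Section 2.5.6 adds: "A process was established to assess family and personal history information provided by participants". Its stated use is to check that the screen suits couples with a relevant history. Defining an analysis group is not mentioned.

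**The concern.** The reason for enrolling these couples and the rule for counting them do not match. They are admitted to be screened for conditions other than the one they know about, yet a result is issued on any reportable finding in a listed gene. If the known condition is on the list, the couple becomes an increased chance couple although screening revealed nothing new.

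This matters most in the economic model. Its increment is the difference between the programme and a world without it. A couple that knew its status beforehand could seek the same reproductive options in that world. Crediting its known-condition result and later choices to the programme overstates what the programme changes. The frequency has the same ambiguity, because it can be read as what screening finds or as what the clinics will see. Section 2.7 says that the results inform an application for public funding, so the two readings should be kept apart.

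**Working it through.** **Inputs from the article**
- Couples: "the study was extended with a revised recruitment target of 8350 couples" (2.4). No precision or power inputs are given for this target, so there is no sample-size figure to reproduce.
- Base frequency p: "it is estimated that 1–2% of reproductive couples have an increased chance of having children impacted by such conditions" (section 1). Section 2.5.6 puts low-chance couples at around 98%, and 1 − 0.98 = 2% agrees with the upper end.

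**Assumptions, not in the article**
- k is the share of all 8350 couples whose already known condition is reported again. I take 0.05% to 0.5%.
- All 8350 couples complete screening.
- p applies to the couples without prior knowledge.

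**Step 1: expected group size and sampling error.** 8350 × 0.01 = 83.5, or 84 couples, and 8350 × 0.02 = 167 couples. The Wilson 95% intervals are 0.81–1.24% for 84/8350 and 1.72–2.32% for 167/8350.

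**Step 2: effect of re-reported known couples.** Observed frequency = k + (1 − k) × p. Share of the increased chance group already known = k / observed frequency. For example, with k = 0.25% and p = 1%: 0.0025 + 0.9975 × 0.01 = 0.012475, or 1.25%; and 0.0025 / 0.012475 = 20%.

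| k (assumed) | Couples | Observed, p = 1% | Already known | Observed, p = 2% | Already known |
|---|---|---|---|---|---|
| 0.05% | 4.2 | 1.05% | 5% | 2.05% | 2% |
| 0.1% | 8.3 | 1.10% | 9% | 2.10% | 5% |
| 0.25% | 20.9 | 1.25% | 20% | 2.245% | 11% |
| 0.5% | 41.8 | 1.50% | 33% | 2.49% | 20% |

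**Step 3: when the shift leaves the interval.** Set k + (1 − k) × p equal to the upper limit and solve for k.
- At p = 1%: k = (1.24 − 1.00) / 0.99 = 0.24%, about 20 couples.
- At p = 2%: k = (2.32 − 2.00) / 0.98 = 0.33%, about 27 couples.

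Below those numbers the shift is within sampling error.

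**Step 4: the economic increment.** Suppose that known couples make the same choices as newly informed ones and would have made them under usual care. Then the already-known share in the table is also the share of the credited effect that the programme did not cause. At k = 0.25% this is 20% (p = 1%) or 11% (p = 2%). If usual care would have changed only some of those choices, the share is smaller.

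**The case against.** The strongest reply is that the article nowhere says known couples are counted together with the rest. It gives other conditions as the reason for enrolling them, describes a history assessment, and limits results to variants meeting study criteria that it does not set out in full. A split by prior knowledge may sit in a fuller plan. This reply stands against any flat claim that the results are pooled. It does not remove the mismatch between the enrolment purpose and the reporting rule, nor between the known couples and the usual-care comparator. Both sides of each are stated in the article.

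Four stronger readings are tempting, and the documents do not support them.

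- **A large inflation of the headline frequency.** Shares of 0.5–1% would give relative increases of 25% (2.49 / 2) to 99% (1.99 / 1). Those shares are guesses from the high end. Not every known couple adds a result: the gene must be listed, the variant reportable and screening completed by both partners. A family history also need not mean that both partners carry a variant. In addition, the 1–2% base is for reproductive couples in general, so adding k on top partly counts known couples twice.
- **A frequency that is not that of a population screen.** A programme offered to everyone would also reach some couples who already know. Only over-representation would bias a population figure. Recruiting through genetics services makes that plausible but does not show it.
- **An all-comers frequency that is wrong for counselling demand.** Section 2.6.5 offers counselling to every couple given an increased chance result, so the all-comers figure is the right one for workload.
- **A distorted anxiety outcome.** The article gives no evidence that known couples respond differently. Its confounder list for the psychosocial analyses is open-ended, so prior knowledge is not ruled out as a covariate.

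**Conclusion.** The concern holds in a limited form. The article enrols couples with prior knowledge, and nothing in its reporting rule, frequency summary or decision tree separates their known condition from a new finding. Followed as written, a known result can count as screen-detected and be credited to the programme. The economic increment is where this does most harm, because the comparator is a world in which the couple could already act.

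The size cannot be derived from the documents. It runs from negligible (about 4 to 8 re-reported couples, within sampling error) to a relative rise of 25–50% in the frequency at about 42 couples (2% to 2.49%, or 1% to 1.50%). About 20 to 27 such couples would be enough to move the estimate past its interval. These figures rest on the assumed share, full screening of 8350 couples and re-reporting of the known condition. The group is small enough that the point should be settled by design and not left to the size of the share.

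**What to change.** 1. Use the family and personal history already assessed (2.5.6) to flag couples whose increased chance was known before the offer. Define the flag from what the couple reported at enrolment, without reference to the screening result, and record which gene or condition was known.
2. Report newly identified and previously known increased chance results separately, beside the all-comers frequency. A finding in a different gene in a flagged couple counts as newly identified, in line with the stated reason for enrolling them. Keep all-comers as the figure for workload.
3. In the decision tree, use newly identified results for the incremental effect, and run the all-comers version as a sensitivity analysis.
4. Repeat the STAI summary for increased chance couples without the flagged couples, as a sensitivity analysis only.

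The cost is one derived flag and a few extra tables, provided that the history entries are held in a form that can be coded. The headline yield may come out slightly lower.

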#### 2.5.3. Developing Education Materials 

Phase 1 also involved developing education materials for rHCPs and participants. rHCP education was initially delivered by the study’s genetic counselors in each state with the use of a PowerPoint presentation either in the rHCP’s clinic or via videoconferencing. The educational content was refined over time with feedback from rHCPs. Once finalized, the PowerPoint presentation was recorded and offered as an option for rHCPs to view in their own time. An online education module was also developed for rHCPs, which comprised written information, videos, infographics and a quiz to self-assess key knowledge concepts. 

An education module for potential participants invited to take part in the study by their rHCP was developed comprising videos, infographics and knowledge questions. The education module informs participants about the study and assists them in deciding whether to have RGCS. The information conveyed outlines: Mackenzie’s story; the study aims; RGCS; the types of genetic conditions included in the screening; inheritance patterns; what it means to be a genetic carrier; how the screening process works; the limitations of the screening; and the possible outcomes of screening, including reproductive options for increased chance couples. A decision aid, which supports decision-making based on consideration of the benefits and limitations of screening with respect to the participant’s views and beliefs, was developed based on previous relevant decision aids [40,41] and is described in detail elsewhere [42]. 

#### 2.5.4. Developing the Enrollment and Participation Process

An online participant portal, including the education module and decision aid, was designed as a convenient way for couples who were invited to take part in the study by their rHCP to enroll and participate. The participant portal was designed by the digital health technology company, Curve Tomorrow, based on the design of the Australian Genomics dynamic consent platform, ‘CTRL’ [43], and with involvement from the MM study team. The participant portal is a web application accessible from smartphones, tablets and computers. Information entered into the participant portal is automatically transferred into the MM electronic study database. Each couple accesses the portal with a unique access code, linked to their rHCP. This access code is provided by the rHCP on a study invitation form (see Supplementary File S2) either in hard copy or electronically. On one side of the invitation form is a brief description of the study and instructions for how to access the participant portal, and on the reverse, is a test request form which is completed by the rHCP to be used for those who accept RGCS. 

To capture the breadth of views on RGCS, the portal was designed to allow for the participation of: those who want to have the screening, those who do not, and those who are unsure. The portal includes: a short introductory video on the study; eligibility questions; a provision of consent to participate in the research; a collection of demographic information; the education module; the optional decision aid [42]; clinical consent for RGCS; an evaluation survey; and optional dynamic consent preferences for data sharing. 

Consent for undergoing RGCS is separate from the consent to take part in the research study, so that the RGCS consent can be provided after the participant has viewed the education module and engaged with the decision aid. The RGCS consent process includes: the purpose of screening; limitations; possible outcomes; the use of information gained through the genetic carrier screening; and data sharing for research. Optional consent preferences for data sharing with other research studies were adapted from the Australian Genomics CTRL platform [43], using a dynamic approach which allows participants to revisit the participant portal and change their preferences at any time.

To maximize accessibility, modified enrollment pathways were developed to support enrollment for people conceiving using a known egg, sperm or embryo donor(s), people with limited English, Aboriginal and Torres Strait Islander people, those who do not have computer/Internet access, and people with disabilities. For people conceiving using a known donor(s) (including the ‘genetic parents’, the person/people who will be parenting/raising the child/ren and the surrogate (if surrogacy is involved)), a separate online enrollment pathway was developed to accommodate and involve the various possible family structures, using inclusive language. A separate online enrollment pathway, with content translated into Arabic and Simplified Chinese (the two most commonly spoken languages in Australia other than English), was also developed for people not fluent in English. A researcher-assisted telephone enrollment pathway was developed for people who require additional support with enrollment, including those who speak other languages and require an interpreter. Hard copy enrollment forms were developed for participants unable to access the online participant portal. To ensure the representation of Aboriginal and Torres Strait Islander people, the study team worked with specific Indigenous health services to develop a tailored recruitment approach involving visual recruitment aids, hard copy enrollment forms and a supported enrollment process. The participant portal was designed in accordance with accessibility principles and standards, to make it accessible to people with disabilities. A free-call study phone number was established and staffed during office hours by the study’s genetic counselors to respond to participants’ questions and provide support as needed. All components of the participant portal and modified enrollment pathways were reviewed by key stakeholders including the Community Reference Group. 

